# Photodynamic therapy for synovial hyperplasia in patients with refractory rheumatoid arthritis: a study protocol for a randomized, double-blind, blank-controlled prospective trial

**DOI:** 10.1186/s13063-021-05640-8

**Published:** 2021-10-09

## Abstract

**Background:**

Persistent synovial hyperplasia with inflammation in rheumatoid arthritis is one of the main pathogeneses of refractory rheumatoid arthritis (RRA). Photodynamic therapy (PDT) causes less trauma than steroid injections or arthroscopic synovectomy while providing stronger targeting and more durable curative effects. The aim of this trial was to evaluate the short-, medium-, and long-term clinical efficacy of PDT when applied as a treatment for RRA synovial hyperplasia and synovitis.

**Methods and analysis:**

This protocol is for a single-center, randomized, double-blind, blank-controlled prospective trial. A sample of 126 RRA patients will be randomly divided into 3 groups: the control group, the “PDT once” group, and the “PDT twice” group, with 42 participants per group. The trial will be conducted by the Rheumatology and Immunology Department of the Integrated Hospital of Traditional Chinese Medicine, Southern Medical University. The Ultrasound Compound Score of Synovitis (UCSS) has been selected as the primary outcome measure. The secondary outcome measures include knee joint clinical assessments, ratio of relapse, duration of remission, Disease Activity Score in 28 joints (DAS28), inflammation indexes, serum concentrations of specific antibodies, and changes in articular structures as detected by X-ray scans in the 48th week. The improvement ratios of the UCSS at the 8th, 24th, and 48th weeks (compared with baseline) reflect short-, medium-, and long-term time frames, respectively.

**Ethics and dissemination:**

The protocol was approved by the Medical Ethics Committee of the Integrated Hospital of Traditional Chinese Medicine, Southern Medical University, China (Approval No. granted by the ethics committee: NFZXYEC-2017-005) and then entered in the Chinese Clinical Trials Registry under registration number ChiCTR1800014918 (approval date: February 21, 2018). All procedures are in accordance with Chinese laws and regulations and with the Declaration of Helsinki by the World Medical Association (WMA). Any modifications of this protocol during execution will need additional approval from the Ethics Committee of our hospital.

**Trial registration number:**

ChiCTR1800014918.

## Background

Rheumatoid arthritis (RA) is a chronic inflammatory disease characterized by persistent joint inflammation and synovial hyperplasia. Without appropriate treatment, patients with RA suffer from joint deformities and progressive functional impairment. Owing to the implementation of the treat-to-target strategy and the availability of biologic therapies, the prognosis for patients with RA has significantly improved [1]. However, some patients with RA respond poorly to multiple drugs (first-line drugs have a tolerance rate of more than 20%, and the effectiveness rate of many biological agents is only 70%) [2]. It is a common phenomenon in ordinary clinical practice for swelling and pain (due to synovitis, including synovial hyperplasia and synovial inflammation) to persist or recurrently relapse in some joints (such as the elbow, knee, and ankle) of RA patients with a low level of main systemic inflammation and arthritis. The persistence of synovitis results in the erosion of cartilage and bone, which further degrades the response to treatment. In the clinic, this type of RA is known as refractory RA (RRA). Aside from conventional medicines that act on the whole body, local injection with hormones in the joint cavity and arthroscopic synovectomy are among the most common methods of RRA therapy, providing short-term relief. However, repeated local injections increase the tendency toward infection and crystallization, causing poor compliance [3]. Arthroscopic synovectomy can also relieve the symptoms temporarily, but patients usually relapse within half a year, sometimes even progressing to a more serious condition because of incomplete resection and the inability to reverse synovial pathology [4]. Therefore, a long-acting therapy administered locally to the joints is urgently needed in the clinic.

Photodynamic therapy (PDT) involves activating a photosensitizer (PS) with a specific wavelength, generating photochemical reactions that are toxic to adjacent tissues [5]. Additionally, utilizing the affinity of PS to hypermetabolic tissues and cells, overproliferated inflammatory cells can be eliminated selectively by the ROS from photoactivated PS molecules, which is a significant advantage of PDT [6].

The goal of applying PDT in the treatment of RRA is to modify the characteristic local pathology-synoviocyte proliferation and inflammatory cell infiltration-through specific PS retention in synoviocytes and inflammatory cells, enabling the selective suppression of synoviocyte proliferation and inflammatory cell infiltration without damage to the normal tissues. PDT has good prospects because of its targeted delivery, high effectiveness, and relatively mild adverse effects; other therapies lack these advantages.

PDT has been used clinically for more than 20 years to treat tumors. Although PDT has shown significant effects in an experimental collagen-induced arthritis (CIA) animal model [7], its effectiveness in the clinical treatment of RA has not been reported until now. To explore the effects of PDT in relieving local synovial proliferation in the knee joints of patients with RRA, we intend to carry out this prospective trial as a pilot study.

## Methods

### Trial design

This is a single-center, randomized, double-blind, blank-controlled trial with 3 groups: the control group, the “PDT once” group, and the “PDT twice” group. The curative effect will be compared statistically across groups. There will be 126 participants in total, with 42 in each group. The trial will be conducted at the Rheumatology and Immunology Department at the Integrated Hospital of Traditional Chinese Medicine, Southern Medical University. Further details can be seen in the flowchart of the trial design in Fig. 1.

**Fig. 1 Fig1:**
[figure not shown]
Trial flow diagram

This study will be carried out according to the Standard Protocol Items: Recommendations for Interventional Trials (SPIRIT) statement, and a SPIRIT checklist has been completed.

### Patients

#### RRA diagnostic criteria

(1) The 1987 American Rheumatism Association (ARA) classification criteria for RA are as follows: (i) morning stiffness in and around joints lasting at least 1 hour before maximal improvement; (ii) Soft tissue swelling or arthritis of 3 or more joints observed by a physician; (iii) Swelling or arthritis of the proximal interphalangeal, metacarpophalangeal, or wrist joints; (iv) Symmetric swelling (arthritis); (v) Rheumatoid nodules; (vi) The presence of rheumatoid factor; and (vii) radiographic erosions and/or periarticular osteopenia in hand and/or wrist joints. Criteria i to iv must have existed for at least 6 weeks. Rheumatoid arthritis is defined as the presence of 4 or more criteria [8]. (2) RA will be classified as RRA if low activity (Disease Activity Score in 28 joints calculated with erythrocyte sedimentation rate (DAS28-ESR)<3.2) or remission (DAS28-ESR<2.6) [9, 10] is not achieved in response to more than 3 months of regular, sufficient treatment, including traditional drugs such as nonsteroidal anti-inflammatory drugs, more than two DMARDs and/or biologic DMARDs, or combined therapy.

#### The inclusion and exclusion criteria

The inclusion and exclusion criteria for the patients are presented in Table 1.

**Table 1 Tab1:** Inclusion and exclusion criteria

*Inclusion criteria*	
*1. Male or female patients aged between 18 and 70 years* *2. Patients who meet the diagnostic criteria for RRA* *3. Patients with swelling of at least one knee for 1 month* *4. Patients with synovial hyperplasia confirmed by ultrasound or MRI: UCSS ≥ 2 points and/or single-site MR scores ≥2 points* *5. Patients who are capable of signing informed consent and completing the trial as required* *6. Patients who have good compliance and will complete follow-up*	
*Exclusion criteria*	
*1. Patients with severe primary diseases, such as disorders of the cardiovascular system, liver, kidneys, brain, or hematopoietic system* *2. Patients with infections or coagulation abnormalities* *3. Breastfeeding or pregnant women* *4. Patients who are allergic to anesthetics or PSs* *5. Patients who have undergone intra-articular drugs injection within the past month* *6. Patients with arthritic knee joints that show osteotropic ankylosis on X-ray examination*	

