### Evaluation procedure

The researchers will record participants’ postoperative improvement and general condition, including body temperature and respiration, pulse, and heart rate, during face-to-face follow-up visits. The items evaluated during each follow-up visit are shown in Table 2. All the data will be uploaded to the case report form (CRF) by rigorously trained data collectors. To reduce the rate of loss to follow-up, we will also communicate with participants by a variety of methods, including WeChat, telephone, text message, and e-mail, to remind them to return for further examination.

**Table 2 Tab2:** Follow-up plan

***Follow-up time***	***Evaluation index***
*Baseline*	*UCSS, clinical evaluation of knee joints, DAS28, antibody levels, inflammation indicators, X-ray, routine blood test, routine urine test, blood biochemical test, infectious disease screening*
*W0* *(first operation)*	*Pathological biopsies of synovial tissue*
*W4±3 d* *(second operation)*	*UCSS, clinical evaluation of knee joints, DAS28, antibody levels, inflammation indicators, pathological biopsies of synovial tissue*
*W8±3 d*	*UCSS, clinical evaluation of knee joints, DAS28, antibody levels, inflammation indicators, blood biochemical test*
*W24±5 d*	*UCSS, clinical evaluation of knee joints, DAS28, antibody levels, inflammation indicators*
*W48±5 d*	*UCSS, clinical evaluation of knee joints, DAS28, antibody levels, inflammation indicators, X-ray*

*W* week, *d* days

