### Outcome and safety measures

#### Outcome measures

Primary outcome measure

The Ultrasound Compound Score of Synovitis (UCSS) will be calculated according to the EULAR-OMERACT combined scoring system for grading synovitis in rheumatoid arthritis [11]. Improvement in the UCSS compared with the control group will be the primary endpoint.
(2)Secondary outcome measures
Clinical evaluation of knee joints: The circumference will be measured 2 cm above the upper edge of the patella, and joint flexion and extension will be measured to assess the range of motion.DAS28-ESR: DAS28-ESR= 0.56 × the total number of tender joints + 0.28 × the total number of swollen joints + 0.70 × ln(ESR) + 0.014 × general health assessment score.Antibody levels: Serum will be collected by centrifugation, and then the RF and anti-CCP antibodies will be detected by a standard commercially available test kit.Inflammation indicators: Serum will be obtained by centrifugation, and then ESR and CRP will be detected by standard commercially available test kits.X-ray: X-rays of the knee joint will be used to evaluate bone destruction.Pathological biopsies of synovial tissue: The synovium of the joint, which will be acquired before laser irradiation during each operation, will be fixed, embedded by dehydration, and sectioned. The synovium will be stained with hematoxylin and eosin for histological evaluation, and synovial histopathology will be observed, including synovial cell proliferation, inflammatory cell infiltration, and angiogenesis (pannus formation). The pathological biopsy of synovial tissue will strictly follow the clinical diagnostic protocol. The research nurses will collect specimens with special specimen boxes, record basic information on the subjects, and then send specimens to the pathology department for testing and preservation as soon as possible.

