#### Statistical analysis

SPSS 20.0 statistical software will be used to analyze the measurement data, described as the means ± standard deviations ($$ \overline{x}\pm s $$), and the main evaluation index (improvement in the UCSS compared with the baseline value) will be analyzed by single-factor variance analysis among the three groups. ANOVA will be used for repeated measurement data of the secondary evaluation indicators to explore the principal and interactive effects of grouping and time. Multiple paired *t*-tests comparing two time points (before and after treatment) will be used to analyze repeated measurements. Single-factor ANOVA will be used to compare the differences at the same time points after treatment between the three groups. Differences will be statistically significant at *P* <0.05.

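### Inclusion 4 could admit patients on MRI alone with a UCSS of 0 or 1, although the primary endpoint is improvement in UCSS

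*Protocol article*

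**What the plan says.** In the protocol article, Table 1 (The inclusion and exclusion criteria), inclusion 4 begins "Patients with synovial hyperplasia confirmed by ultrasound or MRI" and sets the threshold as "UCSS ≥ 2 points and/or single-site MR scores ≥2 points". Either route is enough on its own. No other entry or exclusion criterion sets a minimum UCSS. The nearest is inclusion 3, "Patients with swelling of at least one knee for 1 month", which is a clinical sign and not a score.

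The endpoint is worded in three ways:

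- Outcome measures: "Improvement in the UCSS compared with the control group will be the primary endpoint".
- Statistical analysis: "the main evaluation index (improvement in the UCSS compared with the baseline value) will be analyzed by single-factor variance analysis among the three groups". No baseline covariate is named.
- Abstract, Methods and analysis: a ratio form at weeks 8, 24 and 48, "The improvement ratios of the UCSS at the 8th, 24th, and 48th weeks (compared with baseline".

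Groups and sample size plans on point differences in UCSS between baseline and week 8. The follow-up rows of Table 2 list "UCSS, clinical evaluation of knee joints, DAS28, antibody levels, inflammation indicators" and no MRI, and MRI is not among the outcomes.

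**The concern.** Entry and endpoint are not matched. The plan has its own ultrasound threshold, UCSS of at least 2, but makes it optional by offering MRI as an alternative. A patient who enters by that route may have little or no room to fall on the one scale that decides the trial. The pilot changes used for planning are about 1 point or less, so a floor 0 or 1 point away is not small beside the effect sought.

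Two things are at stake. Patients at the floor contribute little or nothing to the difference between arms, which lowers power. And if the ratio in the abstract were what is analysed, a patient with baseline 0 would have no value at all, while for a patient at 1 each point would count as 100%.

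**Working it through.** **Room to improve.** Assume that the lowest UCSS is 0; the article does not print the range.

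- Baseline 0: the follow-up score is 0 or more, so the reduction (baseline minus follow-up) is 0 or negative. The ratio, reduction divided by 0, is undefined.
- Baseline 1: the largest reduction is 1 point, equal to the pilot mean reduction in the PDT twice group (1.0). The range is restricted, but the patient can respond.
- Baseline 2 or more: at least 2 points of room.

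**Reproducing the plan's sample size.** Inputs from Groups and sample size: pilot changes 0.33, -0.80 and -1.0; SD 0.873; alpha 0.05; power 0.80; 3 groups. The formula is a noncentral F test with noncentrality N×V/σ², where V is the mean squared deviation of the group means and σ² = 0.873² = 0.7621.

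- As printed (control +0.33): mean -0.49; V = (0.82² + 0.31² + 0.51²)/3 = 0.3429. The smallest N in equal groups is 27 (power 84%; 79% at 24), not 99.
- Control -0.33: mean -0.71; V = (0.38² + 0.09² + 0.29²)/3 = 0.0789. At N = 99, noncentrality = 99 × 0.0789/0.7621 = 10.24 and power = 81%. At N = 96 power is just under 80%, so this gives exactly 99.

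Only the changed sign reproduces the stated 99. That conflict is a separate issue, so both cases are carried forward.

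**Effect of patients at the floor.** The share q at UCSS 0 is not given and is assumed. Suppose that they show no change in any arm. Each group mean is then multiplied by (1-q), so V is multiplied by (1-q)². The within-group variance becomes (1-q)×0.7621 + q(1-q)×0.5830, where 0.5830 = (0.33² + 0.80² + 1.00²)/3 is the mean squared group change.

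Example, q = 10%: V = 0.81 × 0.0789 = 0.0639; variance = 0.6859 + 0.0525 = 0.7384; noncentrality = 99 × 0.0639/0.7384 = 8.57; power 73%.

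| Share at UCSS 0 | Power at 99, control -0.33 | Same, SD held at 0.873 | Control +0.33 as printed, SD held |
|---|---|---|---|
| 0% | 81% | 81% | >99.9% |
| 2% | 80% | 80% | >99.9% |
| 5% | 77% | 77% | >99.9% |
| 10% | 73% | 72% | >99.9% |
| 20% | 65% | 61% | 99.8% |
| 30% | 56% | 49% | 98.9% |

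The table describes patients at UCSS 0 only. Patients at 1 would cost less.

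**The case against.** The strongest reply is that the case may hardly arise. Every patient needs a knee swollen for a month, hyperplasia confirmed on imaging, and disease not at low activity despite treatment. An ultrasound score of 0 in such a knee is possible but likely uncommon. This stands, and it puts the lower rows of the table out of proportion to what is likely.

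Four further points also stand:

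- The power loss appears only with a control change that the article does not print.
- The pilot was run under the protocol. If it used the same entry rule, any dilution is already in its means and SD; the article does not say.
- A patient at 0 can still worsen, so zero change in every arm is itself an assumption.
- MRI need not be repeated because it served for entry. Its absence from Table 2 is no fault, and UCSS is measured at baseline and at weeks 4, 8, 24 and 48.

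A reader might also infer that undefined ratios will remove randomised patients from the primary analysis. The documents do not support that. The ratio wording stands only in the abstract, while the sample size rests on point differences and Statistical analysis speaks only of improvement from baseline. What remains is that the article uses two forms without choosing one, and that the entry rule sets no floor. Eligibility is fixed in the protocol, and no later analysis plan can give a patient at the floor room to fall.

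**Conclusion.** The mismatch is real: the entry rule could admit patients with a UCSS of 0 or 1 to a trial judged on UCSS improvement. Its frequency is unknown and probably low. At shares of 2% to 5% the loss is about 1 to 4 percentage points of power (81% to 80% or 77%); at 20% it would be about 16 points (81% to 65%). All of this rests on a scale minimum of 0, a control change of -0.33, no change at the floor in any arm, and no such patients in the pilot. With the printed +0.33, power stays at or above 98.9% up to 30%.

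It would go too far to conclude that the trial is underpowered or that its result would be biased. The share of such patients is not given, and randomisation spreads them over the arms alike, so the effect is dilution. The point is worth acting on because correcting it costs little.

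**What to change.** 1. State in the Abstract, Outcome measures and Statistical analysis that the primary endpoint is the absolute change in UCSS of the study knee, as in Groups and sample size, and not a ratio. Analyse it by ANCOVA with baseline UCSS as covariate. Baseline UCSS is already collected, so this needs no new data.
2. Reword inclusion 4 so that every patient has UCSS of at least 2 in the study knee, which is the plan's own ultrasound threshold, with MRI as supporting evidence only and not required. Replacing the and/or by a plain and would not do, because it would make MRI compulsory. The cost is a few more screen failures and perhaps slightly slower recruitment; the planned 99 and 126 need not change on this account.
3. If the MRI route is kept, report the number with baseline UCSS below 2 in each arm. Baseline adjustment improves precision, but it does not restore room to improve.

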### Groups and sample size

The necessary sample size was estimated to be 99 based on a preliminary trial with a small sample size. During the preliminary phase, eighteen participants were included and randomly divided into 3 groups of 6. According to the protocol, differences in UCSS between week 8 and the baseline value were detected. The mean ± standard deviation of UCSS reduction was obtained at week 8 and week 0 individually: 0.33±0.817, −0.80±0.837, −1.0±1.000. The standard deviation was 0.873, and PASS 11 software was used to estimate the sample size by means of the following formula:

$$ 1-\beta =1- probF\;\left[{F}_{1-a,G-1,N-G,}\;\left(G-1\right),N-G, NV/{\sigma}^2\right] $$

The significance level, *α*, was set to 0.05; the power of a test, 1 − *β*, was 0.80; the number of groups, *G*, was 3; *N* represents the sample size; *V* represents the variance of the group averages, $$ V=\Sigma \left({\left({\mu}_i-\overline{\mu}\right)}^2\right)/G $$; σ represents the standard deviation.

A total of 126 participants will be included to allow for 20% loss to follow-up. There will be 3 groups:
Control group: (*n*=42) These individuals will receive micro-arthroscopic surgical procedures twice (day 0 and 4th week), and 0.9% saline will be administered instead of PS.PDT once group: (*n*= 42) Participants will receive PDT on day 0, followed by 0.9% saline administration instead of PS in the 4th week.PDT twice group: (*n*=42) Individuals will receive PDT twice: once on day 0 and once in the 4th week.

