## Discussion

Traditional drugs, including nonsteroidal anti-inflammatory drugs, steroids, and disease-modifying antirheumatic drugs (DMARDs), have rapidly developed in the past 10 years and can control the general condition of most RA patients. However, the curative effects are poor in some RA patients, which reduces their quality of life and greatly increases the difficulty of RA treatment. Although refractory joints can be treated with local steroid injections or arthroscopic synovectomy, these treatments have substantial shortcomings, and the pain may not be fully resolved. As a potential therapy for the treatment of synovial hyperplasia in RRA, PDT causes less trauma than steroid injections or synovectomy while providing stronger targeting, fewer side effects, and more accurate curative effects. Patients tend to tolerate PDT treatment better than these alternatives. PDT has prospects for broad application and has demonstrated promising effects on synovitis, but there remain some problems to be solved.

We have determined that refractory synovitis is essential in RRA, and early intervention in long-term RA can be useful for reducing the proliferation and migration of synoviocytes and inhibiting inflammatory cell infiltration. The cytotoxic and immunoreactive effects of PDT can inhibit synovial hyperplasia and pannus formation, thereby reducing cartilage and bone destruction, which is critical for RRA treatment. In clinical practice, we found that the irradiation dose and the duration of treatment and scope of PDT are difficult to establish, and single therapy cannot completely eliminate synovial hyperplasia. The curative effect requires long-term clinical experience to be defined.

To date, almost all studies on the possibility of PDT to treat RA have consisted of basic research and experiments in animal models of arthritis, which have confirmed the effect of PDT. There is a lack of research on clinical efficacy evaluation until now. In view of this, this study aims to clarify the short- and long-term clinical efficacy of PDT in the treatment of RA synovitis, explore the frequency and duration of treatment, and finally form a practical standard therapy for RRA synovial hyperplasia.

We believe that with an increasing number of basic research and clinical trials, the long-term efficacy and technical problems of PDT in the treatment of RRA synovial hyperplasia will be addressed and PDT will be widely applied.

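### The printed pilot means and the stated sample size of 99 are incompatible under the protocol's own formula: as printed they need 27, and a missing minus sign on the first mean is the likely cause

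*Protocol article*

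**What the plan says.** All the inputs are in the protocol article, Methods, Groups and sample size.

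- Target: "The necessary sample size was estimated to be 99 based on a preliminary trial with a small sample size".
- Pilot results, from 18 participants in three groups of six: "UCSS reduction was obtained at week 8 and week 0 individually: 0.33±0.817, −0.80±0.837, −1.0±1.000". The sentence before this describes the quantity as the difference in UCSS between week 8 and baseline. The three values carry no arm labels.
- Spread and software: "The standard deviation was 0.873, and PASS 11 software was used to estimate the sample size".
- Design values: "The significance level, *α*, was set to 0.05"; "the power of a test, 1 − *β*, was 0.80"; "the number of groups, *G*, was 3".
- Formula: power of the one-way F-test from the noncentral F distribution with noncentrality NV/σ², where V is the sum of squared deviations of the group means from their average, divided by G.
- Enrolment: 126, or 42 per group, to allow for 20% loss to follow-up.

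The Statistical analysis section plans a one-way analysis of variance across the three groups for the main index, so the formula matches the planned primary test.

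**The concern.** The article prints the complete formula and every input, so a reader should be able to reproduce 99. The printed means are far apart relative to the standard deviation: the first is positive, the other two are negative, and the largest gap is 1.33 against an SD of 0.873. A difference of that size needs a much smaller trial than 99.

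This is the trial's only sample-size justification. The sign of the first mean decides whether the pilot controls got worse or better by about a third of a point, and hence how large an effect the trial assumes. It also decides whether the enrolled number follows from the stated 80% target or far exceeds it, in a trial where every participant has two arthroscopic procedures.

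**Working it through.** **Inputs** (all from Groups and sample size): means 0.33, −0.80, −1.00; σ = 0.873, so σ² = 0.7621; α = 0.05; target power 0.80; G = 3; equal allocation.

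**Formula.** Power = P(F′ > F crit), where F′ is noncentral F with 2 and N − 3 degrees of freedom and noncentrality λ = N·V/σ², and F crit is the central 95% point.

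**1. Means as printed**
- Average: (0.33 − 0.80 − 1.00)/3 = −0.49. Deviations: 0.82, −0.31, −0.51.
- V = (0.6724 + 0.0961 + 0.2601)/3 = 0.3429. Effect size √V/σ = 0.671.

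| N | per group | λ | power |
|---|---|---|---|
| 24 | 8 | 10.80 | 78.6% |
| 27 | 9 | 12.15 | 84.2% |
| 99 | 33 | 44.54 | > 99.99% |

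The required total is 27, not 99 (99/27 = 3.7).

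**2. First mean taken as −0.33**
- Average: (−0.33 − 0.80 − 1.00)/3 = −0.71. Deviations: 0.38, −0.09, −0.29.
- V = (0.1444 + 0.0081 + 0.0841)/3 = 0.0789. Effect size 0.322.

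| N | per group | λ | power |
|---|---|---|---|
| 96 | 32 | 9.93 | 79.9% |
| 99 | 33 | 10.24 | 81.2% |

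This gives exactly the stated 99.

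**3. Other routes to 99**
- Changing the sign of the second or the third mean instead gives N = 18.
- Reversing all three signs leaves V, and so N = 27, unchanged.
- With the printed means, varying alpha (0.05 to 0.01), power (0.80 or 0.90), the SD (0.817 to 1.0) and the divisor of V gives totals from 18 to 69.
- Pairwise t-test sizing on the printed means gives 21 to 51 in total for comparisons with control and at least 900 for once versus twice.
- Reaching 99 from the printed means would need an SD of about 1.85.
- Solving for the first mean with the other two fixed also yields −1.47. That is only the mirror image of −0.33 about the average of the other two (−0.90) and is not a sign change.

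**4. Standard deviation.** The equal-weight pool of the three printed SDs is √((0.817² + 0.837² + 1.000²)/3) = 0.888, slightly above the stated 0.873. With 0.888 the printed means still need 27, so this does not explain the gap.

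**5. Loss to follow-up.** 33/0.8 = 41.25, rounded up to 42 per group and 126 in total. This step reproduces.

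**6. Pairwise power at 33 per arm** (secondary; two-sided 0.05, SD 0.873, no multiplicity adjustment)

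| Comparison | first mean −0.33 | first mean +0.33 |
|---|---|---|
| twice vs control | 87% (difference 0.67) | > 99.9% (1.33) |
| once vs control | 58% (0.47) | 99.9% (1.13) |
| once vs twice | 15% (0.20) | 15% (0.20) |

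**The case against.** The strongest reply is that this is one dropped minus sign. The exact match at −0.33 supports that. On that reading 99, 126 and 80% power for the F-test all stand, and nothing in the conduct of the trial changes. This is fair as to likelihood, but it does not remove the contradiction: the paragraph as printed is wrong somewhere, and only the pilot data can show where.

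It can also be said that calling the values a reduction is loose wording for week 8 minus baseline, so that negative means improvement. That is plausible in context. It does not rescue 99, because a change of convention reverses all three signs and leaves N at 27.

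A reader might infer more than the document supports, in three ways.

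- That the trial is underpowered, or that the 80% applies to no comparison it plans. The Statistical analysis section makes the three-group analysis of variance the primary test, and at 99 that test has at least 81% power under either sign.
- That comparisons with control are weak whatever the sign. The 58% for once versus control arises only under −0.33; with the printed +0.33 it is 99.9%.
- That the trial promises a powered comparison of once with twice. The Discussion says only that the study will "explore the frequency and duration of treatment, and finally form a practical standard therapy for RRA synovial hyperplasia". Power for that contrast is about 15% under either sign, but no passage claims otherwise, so it is context and not an error.

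**Conclusion.** The point holds as an internal contradiction: under the protocol's own formula, the printed means give 27 and the text says 99, a factor of 3.7 and far beyond rounding. Either a printed pilot mean or the stated sample size is wrong. A missing minus sign on the first mean is the likely cause, since that single change gives 99 exactly.

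This conclusion rests on two assumptions. The means are unlabelled, so identifying the first as control relies on the order in which the arms are listed; the figures 27 and 99 do not depend on the label. And the statement that nothing else gives 99 covers only single sign changes and the standard variants listed above.

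If +0.33 proves correct, the stated 80% target does not justify 99. It would be wrong to assert that the trial is oversized before the pilot data are checked, because that is the less likely branch.

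**What to change.** Check the pilot records, then correct the sample-size paragraph to match.

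- **If the first mean is −0.33:** label the three arms, print changes (week 8 minus baseline) of −0.33, −0.80 and −1.00, keep 99 and 126, and state about 81% power for the three-group F-test.
- **If it is +0.33:** either state that 99 gives more than 99.99% power on these inputs, or replace 99 with the re-derived number. If 99 is kept, give the reason for exceeding the 80% target.
- **In both cases:** describe the quantity as a change from baseline, not a reduction, so that the direction is clear.

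Optionally, add the pairwise powers for the sign that proves correct, and say that once versus twice is estimated with a confidence interval and not powered.

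The cost is a look-up in data already held and one corrected paragraph. No extra patients and no design change are needed.
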